## Abstract

**Background:**

Many cancer survivors suffer a range of physical and psychological symptoms which may persist for months or years after cessation of treatment. Despite the known benefits of exercise and its potential to address many of the adverse effects of treatment, the role of exercise as well as optimum duration, frequency, and intensity in this population has yet to be fully elucidated. Many cancer rehabilitation programmes presented in the literature are very long and have tight eligibility criteria which make them non-applicable to the majority of cancer survivors. This paper presents the protocol of a novel 8-week intervention which aims to increase fitness, and address other physical symptoms in a heterogeneous cancer survivor population.

**Methods/design:**

The aim is to recruit 64 cancer survivors 2-6 months after completion of chemotherapy, usually adjuvant, with curative intent. Subjects will be recruited through oncology clinics in a single institution and randomised to usual care or an exercise intervention. The exercise intervention consists of two specifically tailored supervised moderate intensity aerobic exercise sessions weekly over 8-weeks. All participants will be assessed at baseline (0 weeks), at the end of the intervention (8 weeks), and at 3-month follow-up. The primary outcome measure is fitness, and secondary patient-related outcome measures include fatigue, quality of life, and morphological outcomes. A further secondary outcome is process evaluation including adherence to and compliance with the exercise program.

**Discussion:**

This study will provide valuable information about the physical outcomes of this 8-week supervised aerobic programme. Additionally, process information and economic evaluation will inform the feasibility of implementing this program in a heterogeneous population post cessation of chemotherapy.

**Trial Registration:**

NCT01030887

## Background

The benefits of exercise in the general population are well established [1,2]. The current physical activity recommendation for adults aged between 18-65 years to promote and maintain health is to accumulate at least 30 minutes of moderately intense physical activity on at least five days of the week. Sedentary behaviour, such as time spent sitting is positively associated with coronary heart disease risk factors, obesity, and development of the metabolic syndrome [3,4]. More recently, the link between sedentary behaviour and the development of certain cancer types has been reported.

Newer evidence indicates that increased physical activity after a cancer diagnosis may reduce the risk of cancer recurrence and mortality [5-7]. Cancer survivors are at risk of developing new primary tumours as well as secondary tumours and chronic diseases such as cardiovascular disease, osteoporosis, and diabetes [8]. This increased risk across conditions may be genetic or treatment-related but may also reflect the fact that common life-style factors, including a sedentary lifestyle, increase the risk for more than one disease [8].

Physical activity is also advocated during and after the treatment for cancer. However, the adverse effects of treatment which frequently impact on physical functioning and quality of life, may persist even years after treatment [9-11], and must be taken into account. Many treatments for cancer are toxic, increasing the risk for a number of medical problems and late treatment effects such as neuropathy [12] and cardiovascular disease [12-14]. Cardiopulmonary capacity may also be compromised in cancer survivors because of side effects of therapy regimens such as weight gain and inactivity secondary to treatment. The reduction in cardiopulmonary capacity may lead to decreases in quality of life [15,16]. A downward trajectory in aerobic fitness is generally observed, possibly caused by chemotherapy and associated side-effects such as anaemia, tachycardia, dehydration, and cardiac dysfunction [17,18].

Other cancer survivors experience somatic symptoms which may also persist for years after treatment such as chronic fatigue [19,20], weight gain [19], loss of muscle strength [21,22] and difficulty sleeping [20]. Physical and functional well-being are essential dimensions for overall quality of life [23], and poor physical functioning may explain some of the psychological distress experienced by cancer survivors [21,22].

The rationale for physical activity interventions following cancer diagnosis includes minimizing biological processes associated with tumour growth [24], enhancing behavioural changes to try to minimise lifestyle risk factors for recurrence of cancer [25], and improving psychosocial factors during and after cancer [26]. The main physiological outcomes of physical activity after cancer are improved fitness and physical functioning [27,28], reduced fatigue [29], and modestly decreased weight and body fat [30].

Even though there is strong evidence for the benefits of physical activity aftercancer-treatment, the majority of cancer survivors do not meet public health guidelines for levels of physical activity necessary for health-related benefits [31-34]. Clearly, there is a need to promote physical activity, but the optimal intervention modality, intensity, training and duration are still unknown.

Many programmes in cancer rehabilitation are mainly based on psychotherapy or social support. Such therapies however do not usually deal with the physical problems encountered by many patients, such as fatigue, loss of functional capacity and weight gain [35]. Many cancer rehabilitation programs and/or trials which include a physical rehabilitation are lengthy in duration, extremely intensive [36] and have tight eligibility criteria. They would be expensive to translate into general clinical practice or to apply to the general cancer survivor population.

We have therefore devised a RCT to evaluate the effectiveness and feasibility of an 8-week intervention to improve fitness and other secondary outcomes.

## Methods/Design

### Study design

This will be a single-blind 2 arm pragmatic randomised controlled trial of individually prescribed exercise in a class setting versus usual care.

### Primary aims

#### Outcome evaluation

To examine the effects of a supervised exercise program commenced within 2-6 months after completion of chemotherapy and/or radiotherapy with curative intent on cardio-respiratory fitness, and on quality-of-life, fatigue and morphological outcomes.

#### Process Evaluation

As this is a feasibility study, an additional aim is to determine the acceptability of the programme, as well as adherence and compliance with the prescribed duration and intensity during supervised exercise sessions.

### Patient Recruitment

Participants will be sourced from the institutional cancer database, by invitation from study personnel in cancer clinics and directly from the oncology service in St. James's Hospital, Dublin, Ireland. Study personnel will provide further information to these patients and assess them for eligibility. Ethical approval has been approved from the institutional Research Ethics Committee and informed consent will be gained from each participant prior to study inclusion.

Aerobic fitness will be measured using the Modified Bruce treadmill test and those with aerobic fitness levels average or below age- and gender norms [37] and meeting other inclusion criteria will be invited to participate in the study. Subjects scoring average or below for age and gender cut-off levels according to the Modified Bruce Protocol, will be randomized to the exercise intervention or usual care.

### Inclusion criteria

(i) Diagnosis of solid tumour and completion of adjuvant chemotherapy or radiotherapy with curative intent within the preceding 2-6 months. Patients who have received neoadjuvant chemotherapy or chemoradiotherapy followed by surgery will also be eligible. Patients continuing onto adjuvant hormone therapy and anti-Her2 directed therapy are eligible

(ii) Ability to understand English

(iii) Willing to be randomised

(iv) Medical clearance to exercise

(v) Age 21-69

(vi) Fitness level average, fair or poor according to certain pre-determined cut-off points for age and gender[37]

(vii) Willing and able to attend supervised exercise sessions twice weekly for a period of 8 weeks, with an intention of achieving > 90% attendance

(viii) LVEF > 50% and not < 20% worse than baseline in applicable patients

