### Exclusion criteria

(i) Evidence of active cancer

(ii) Chronic medical and orthopaedic conditions that would preclude exercise (eg uncontrolled congestive heart failure or angina, recent MI, breathing difficulties requiring oxygen use or hospitalization)

(iii) On beta-blocker medication

(iii) Prior history of another cancer in previous 5 years (exception: non-melanoma skin cancer and non-invasive cancer of the cervix)

(iv) Confirmed pregnancy

(v) Dementia or psychiatric illness that would preclude ability to participate in study

(vi) Incomplete haematological recovery after chemotherapy (WCC < 3, Hb < 10 or Platelets < 100)

(vii) BMI > 35

(viii) LVEF post chemotherapy < 50% or > 20% deterioration of baseline compared to LVEF before systemic treatment. LVEF criteria are applicable in patients who have received systemic therapy (eg anthracycles, Her-2 antagonists etc) deemed in normal clinical practice to have a potential effect LVEF and in whom the LVEF will have been measured before systemic treatment and at end of chemotherapy

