### Statistical analysis

Randomization will be by a computer-generated random numbers list (GraphPad Software, San Diego, CA) with intention-to-treat as the primary analysis and per protocol as the secondary analysis.

Assuming a difference of 5 mL/kg/min^-1^, with a SD of 6.5, and a 5% significance (two-sided) and 80% power, 28 participants would be required per group. However, the goal would be to accrue 32 subjects to allow for a 15% drop out rate and subgroup analyses. One year will be allowed for accrual of participants. The drop-out rate is calculated to include patients who are unfortunately diagnosed within 3 months of the final assessment as having a relapse of their cancer. As occult return of cancer could have a negative impact on fitness and capacity to exercise, these patients' data will be excluded from the primary outcome measure but included in the process analysis. The same will be done for the data of any participant on anti-Her2 therapy in whom an LVEF assessment during the study or within 3 months of the end of the study has a drop in LVEF to < 50% or by > 20% compared to baseline, as, similarly, occult ongoing myocardial toxicity could have a negative impact on fitness.

We will provide descriptive data and 95% CIs for all possible comparisons. For our primary analysis, we will use the intent-to-treat principle and for the secondary analysis, per-protocol analysis. In sensitivity analyses (intent-to-treat), the impact of missing values will be studied by using a range of imputed change scores for missing values, and by analysing those subjects who provide complete data. Repeated measured of analysis (ANOVA) will be used across more than two time points for continuous data. Mixed-model analysis will be used to model each outcome measure at three (or two) time points and compare the differences across groups over time for non-continuous data. We will use t-tests between 2 groups when data are normally distributed and the Mann-Whitney U test will be used when data are non-normally distributed. The Chi-squared test will be used for categorical data. Tests for interaction will be carried out for the effect of gender and type of cancer.

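### Read plainly, the LVEF inclusion criterion (viii) runs opposite to exclusion criterion (viii), and its 20% has no stated unit

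*Protocol article*

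**What the plan says.** Three places in the protocol article set an LVEF rule.

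- Inclusion criteria (viii): "LVEF > 50% and not < 20% worse than baseline in applicable patients".
- Exclusion criteria (viii): "LVEF post chemotherapy < 50% or > 20% deterioration of baseline compared to LVEF before systemic treatment". The same item defines who is covered: "LVEF criteria are applicable in patients who have received systemic therapy (eg anthracycles, Her-2 antagonists etc"), provided LVEF was measured before that therapy and again when chemotherapy ended.
- Statistical analysis: the primary-outcome data of a participant on anti-Her2 therapy are left out if an LVEF assessment in the study, or in the three months after it, "has a drop in LVEF to < 50% or by > 20% compared to baseline".

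Inclusion criteria (i) adds: "Patients continuing onto adjuvant hormone therapy and anti-Her2 directed therapy are eligible".

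**The concern.** Someone 5% worse than baseline is less than 20% worse. A clause that requires a patient not to be less than 20% worse therefore rejects that person, and it rejects anyone whose LVEF has not changed. The exclusion criterion points the other way and turns patients away for a fall above 20%. A screener who applies both sentences as printed would refuse patients with stable LVEF, among them the anti-Her2 patients whom inclusion (i) says may enter.

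What is at stake is who can be recruited from the subgroup covered by the LVEF criteria. Separately, because the 20% has no unit, two screeners could classify the same patient differently even after agreeing on the direction.

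**Working it through.** **Inputs.** The three LVEF rules quoted above. Let B be the comparison LVEF, P the post-treatment LVEF and d the fall. On a relative reading d = 100 × (B − P)/B. On a points reading d = B − P. The article gives no LVEF values, so the values of B and P below are illustrative assumptions.

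**1. Direction.**
- Inclusion (viii), plain reading: P > 50 and not (d < 20), that is, P > 50 and d ≥ 20.
- Not excluded by (viii): not (P < 50 or d > 20), that is, P ≥ 50 and d ≤ 20.
- Both together: P > 50 and d = 20 exactly.

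With B = 65 and the relative reading:

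| P | d | Inclusion (viii), plain reading | Exclusion (viii) |
|---|---|---|---|
| 65 | 0 | fails | not excluded |
| 60 | 5/65 = 7.7% | fails | not excluded |
| 52 | 13/65 = 20% | meets | not excluded |
| 51 | 14/65 = 21.5% | meets | excluded |

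**2. Check on a grid.** Take whole-number pairs with B from 50 to 80 and P from 30 to 80, which is 31 × 51 = 1,581 pairs. The grid weights all pairs equally. It shows the logic and does not estimate a share of patients.

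| Reading of 20% | Pairs passing the exclusion | Also meeting inclusion, plain reading | Also meeting inclusion if its direction matches the exclusion |
|---|---|---|---|
| Relative | 824 | 4 (65→52, 70→56, 75→60, 80→64) | 811 |
| Points | 906 | 10 (71→51 up to 80→60) | 885 |

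If the inclusion is read as relative and the exclusion in points, 78 pairs meet both, but unchanged or mildly reduced LVEF still fails inclusion.

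**3. The 50% boundary.** The shortfalls in the last column are 824 − 811 = 13 and 906 − 885 = 21. All of these pairs have P exactly 50, which does not meet the inclusion level but does not trigger the exclusion.

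**4. Unit of the 20%.**
- From B = 65 the limit is 0.8 × 65 = 52 (relative) or 65 − 20 = 45 (points).
- In points, 70 − 20 = 50. For any B up to 70, a fall of more than 20 already puts P below 50, so the change clause adds nothing to the level clause.
- On the relative reading, the change clause starts to matter above B = 50/0.8 = 62.5.
- A patient going from 65 to 51 is excluded on the relative reading (21.5%) and not excluded on the points reading (14).

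**5. Comparator.** Exclusion (viii) compares with LVEF before systemic treatment. Inclusion (viii) and Statistical analysis say only baseline, a word that the Assessment section uses for week 0.

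**6. Sample size, for context.** The inputs are "Assuming a difference of 5 mL/kg/min^-1^, with a SD of 6.5" and "5% significance (two-sided) and 80% power, 28 participants would be required per group". A two-sample t-test gives 27.5, so 28 per group, as stated. LVEF does not enter this calculation, so the point leaves it unchanged.

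**The case against.** The strongest reply is that the clause can be parsed differently. LVEF is the subject of both halves, so the second half may mean that LVEF is not below the value lying 20% under baseline. That is a fall of at most 20%, in full agreement with exclusion (viii). The exclusion gives direction, timing and coverage, Statistical analysis uses the same direction, and inclusion (i) shows that an almost empty subgroup was not intended. Most staff would probably follow the exclusion. This stands as an account of intent and lowers the practical effect. It does not cure the sentence, because the parse needs words that are not there, and an eligibility rule should not depend on screeners setting aside one of two printed criteria.

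The reply is also right about four stronger conclusions that a reader might draw:

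- *Unsuitable patients could enter.* The documents do not support this. Exclusion (viii) is intact and inclusion (iv) separately requires medical sign-off for exercise, so no reading of inclusion (viii) admits a patient whom the exclusion bars.
- *The inverted clause decides whose data are removed from the primary analysis.* It does not. Statistical analysis has its own rule, in the same direction as the exclusion and limited to participants on anti-Her2 therapy. Only the unit and comparator of the 20% carry over.
- *The status of a patient with LVEF of exactly 50% is undetermined.* It is determined: every inclusion criterion must be met, so that patient is ineligible. The unmatched boundaries are a drafting flaw.
- *The unit is entirely open.* The exclusion wording leans towards a proportion of baseline, and the redundancy of a points reading up to a baseline of 70% leans the same way. Neither is a definition.

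That the article condenses a fuller protocol is no answer on direction, since two stated criteria conflict and nothing is missing.

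**Conclusion.** The point holds as a wording contradiction in an operative eligibility rule. On the plain reading, inclusion (viii) and exclusion (viii) together admit only a fall of exactly 20% among patients to whom the LVEF criteria apply, contrary to inclusion (i). The likely cause is a reversed sign or double negative.

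A reader might infer that almost no such patient would in fact be enrolled. The documents do not show that: the result rests on the literal parse, a charitable parse removes it, and the number of patients covered is not given. The error can only over-restrict entry. It is not a safety failure, and it changes neither the sample size nor the primary analysis.

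The unmatched 50% boundaries and the undefined unit and comparator of the 20% are secondary. They would remain even under the charitable parse.

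**What to change.** The investigator should reconcile inclusion (viii) with exclusion (viii) so that the LVEF criterion is stated once, with a consistent direction and a single treatment of the 50% boundary, and is referred to from the other list. The 20% should be declared either relative or in percentage points, and its comparator named (LVEF before systemic treatment or at week 0), in that criterion and again in the data-exclusion rule under Statistical analysis. No threshold is proposed here; that choice belongs to the investigator.

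The cost is a short protocol amendment, with no extra tests and no change to the sample size.

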### Exclusion criteria

(i) Evidence of active cancer

(ii) Chronic medical and orthopaedic conditions that would preclude exercise (eg uncontrolled congestive heart failure or angina, recent MI, breathing difficulties requiring oxygen use or hospitalization)

(iii) On beta-blocker medication

(iii) Prior history of another cancer in previous 5 years (exception: non-melanoma skin cancer and non-invasive cancer of the cervix)

(iv) Confirmed pregnancy

(v) Dementia or psychiatric illness that would preclude ability to participate in study

(vi) Incomplete haematological recovery after chemotherapy (WCC < 3, Hb < 10 or Platelets < 100)

(vii) BMI > 35

(viii) LVEF post chemotherapy < 50% or > 20% deterioration of baseline compared to LVEF before systemic treatment. LVEF criteria are applicable in patients who have received systemic therapy (eg anthracycles, Her-2 antagonists etc) deemed in normal clinical practice to have a potential effect LVEF and in whom the LVEF will have been measured before systemic treatment and at end of chemotherapy

### Assessment

Post randomization follow-up will be at baseline (week 0), end programme (8 weeks) and 3 month follow-up.

#### Baseline Characteristics

Cancer grade, stage, surgical management, treatment regimen (chemotherapy, radiation therapy, hormonal therapy) and previous medical history will be recorded by accessing medical charts. Socio-demographic variables recorded will include age, gender, ethnicity, employment status, smoking, and alcohol habits accessed from medical charts and/or subjective interview.

#### Body Composition

Anthropometric parameters will be measured at baseline, 8 weeks and at 3 months. Body weight will be measured to the nearest gram (g) using a standardised digital scales. Standing height will be measured, without shoes, to the nearest millimetre (mm) using stadiometer. BMI will be calculated by dividing weight in kilograms by height in metres squared.

Lean body mass will be evaluated using bioimpedence (Tanita). Waist Circumference will be measured as per the protocol outlined in the ACSM Resource Manual [38].

#### Cardiovascular Parameters

Resting heart rate will be measured after a five minute rest period in a seated position. Heart rate reserve will be calculated by subtracting the resting heart rate from peak heart rate during exercise. Oxygenation saturation will be monitored using a finger pulse oximeter.

Blood pressure (BP) will be measured using the auscultatory method in accordance with the Joint National Committee on Prevention, Detection, Evaluation, and Treatment of High Blood Pressure guidelines.

#### Outcome Measures

##### Primary Outcome measure: Fitness

Physical fitness will be measured by the Modified Bruce Protocol. A sub-maximal test was chosen over a maximal test for this population because of safety and motivational concerns [39]. Verbal encouragement during the exercise test will be standardised.

##### Secondary outcomes

##### Quality of life

We will use the FACT-G scale (general) (and the physical functional measure of the SF-36. Many uncontrollable factors influence QOL during and after chemotherapy and a global measure of cancer-specific QOL may be too broad to detect the likely narrower effects of exercise training, therefore a more appropriate and realistic primary end-point in exercise trials may be the functional component of QOL [40]. A statistically significant increase of greater than 4.0 points on the FACT scale represents a clinically meaningful improvement in quality of life from exercise [41].

The Fact-G (version 4) is a 27-item questionnaire divided into 4 primary QOL domains: physical well-being, social/family well-being, emotional wellbeing, and functional well-being and an overall quality of life level is also yielded. The FACT-G takes about 5 minutes to complete and has been written at the 6th grade level. This questionnaire was initially developed by Cella et al. 1993 and has been validated in a mixed cancer population [42]. Patients rate all items using a 5-point rating scale ranging from "not at all" to "very much". Strong concurrent validity is reported by strong Pearson correlations with the Functional Living Index - Cancer (0.79) and the patient-completed version of the QL index (0.74). Using the global rating of change (GRC) scale as an anchor, Cella et al proposed that a clinically meaningful change corresponds to a total FACT-G raw score in the range of 5-7 points [43]. A 2008 review by Victorson et al., reported the average reliability of the FACT-G to be 0.88 with the reliability of subsets ranging from 0.71-0.83.

The SF-36v2 is a widely used generic measure of health status. Psychometric properties of the SF-36 have been well established [44]. Thirty five of the 36 items are grouped into eight scales that address health constructs considered to be important to most health care situations: physical functioning, role limitations (physical problems), bodily pain, general health, vitality, social functioning, role limitations (emotional problems), and mental health We will use the Physical Health measure only of the SF-36 for the purposes of this study.

